#### Participant inclusion criteria

The included participants must meet all the following criteria: (a) patients aged between 18 and 65 years, male or female; (b) patients who meet IBS-D Rome IV diagnostic criteria [9]; (c) patients who meet Liver Depression and Spleen Deficiency Syndrome (Ganyu Pixu Zheng) from the diagnostic criteria for TCM syndromes (2017) [26]; (d) irritable bowel syndromes symptom severity score (IBS-SSS) ≥ 75 points; (e) patients who have not taken any medications related to the treatment of IBS-D at least 1 week before enrolling the trial and have not participated in other ongoing trials; (f) patients who have had a colonoscopy within 1 year and had an examination report; (g) patients who have accepted to participate in the trial voluntarily and have signed the informed consent form. The informed consent process complies with Good Clinical Practice (GCP); (h) long-term (at least 6 months) residence in the place where the treatment is given.

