#### Concomitant treatment

If the participant is unable to tolerate the IBS-D symptoms or is dissatisfied with the therapeutic effects of TXYF during the treatment, pinaverium bromide (the first-line recommended drug in American Gastroenterological Association Institute Guidelines on the Pharmacological Management of Irritable Bowel Syndrome [27]) or other medications recommended by guidelines will be allowed to be taken by the patient. No matter what medications the patient uses, the medication’s name, dosage and duration of administration will be recorded in detail in CRF.

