#### Statistical description and statistical analysis methods

With regard to continuous outcomes, Q-Q plots will be used to evaluate normality assumptions. Continuous outcomes conforming to the normal distribution will be presented as mean ± standard deviation (SD) and non-conforming to the normal distribution will be presented as median and interquartile range (IQR) [41]. For both primary continuous outcomes and secondary continuous outcomes, simple or multiple linear regression will be applied to estimate the difference between TXYF group and placebo group. Two preadjusted analyses will be conducted, if appropriate. The first preadjusted regression analysis included only baseline variables (e.g., age, gender, smoking and drinking). The second preadjusted analysis will also adjust for concomitant treatment, a variable thought to be associated with outcome but not affected by treatment allocation.

Categorical data will be expressed by the number and percentage of occurrences. For primary and secondary categorical outcomes, differences will be compared using chi-squared tests and, if appropriate and necessary, logistic regression. The preadjusted analyses will be conducted that adjust for the same covariates as those described for the continuous outcomes.

Estimates of treatment effect will be reported with 95% confidence intervals. Two-tailed *P*-values ≤ 0.05 will be considered statistically significant.

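### The second adjusted analysis conditions on concomitant treatment as if allocation could not affect it, although the protocol makes its use depend on symptoms and satisfaction after randomisation

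*Protocol article*

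**What the plan says.** The protocol's section on statistical description and analysis methods plans simple or multiple linear regression for continuous outcomes and chi-squared tests, with logistic regression where needed, for categorical ones. It then adds: "Two preadjusted analyses will be conducted, if appropriate". Of these, "The first preadjusted regression analysis included only baseline variables", with age, gender, smoking and drinking as examples. The second will also "adjust for concomitant treatment, a variable thought to be associated with outcome but not affected by treatment allocation". The categorical analyses will "adjust for the same covariates as those described for the continuous outcomes", so the covariate also reaches the IBS-SSS response rate.

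The Concomitant treatment section sets the condition for use: "If the participant is unable to tolerate the IBS-D symptoms or is dissatisfied with the therapeutic effects of TXYF during the treatment", pinaverium bromide "or other medications recommended by guidelines will be allowed to be taken by the patient". Name, dosage and duration go into the CRF. Inclusion criterion (e) admits "patients who have not taken any medications related to the treatment of IBS-D at least 1 week before enrolling the trial".

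**The concern.** A covariate can be added to a randomised comparison without changing what is estimated when it is fixed before randomisation or cannot respond to treatment. The protocol claims the second property for concomitant treatment, but its own rule for use points the other way. A participant takes these drugs because symptoms are bad or the study product seems not to work, and both depend on what the allocated product does.

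At stake is the meaning of one pre-specified result on the primary outcome. The protocol states an ITT principle, which targets the effect of allocation. A model that holds later IBS medication constant does not generally estimate that effect. Nor does it isolate the effect of TXYF apart from other drugs, because symptom severity drives both their use and the final score. A reader told that the covariate is unaffected by allocation would have no reason to discount the result.

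**Working it through.** **Is it a post-randomisation variable?** The plan gives no figure for this point to reproduce, so the first check sets the sections side by side.

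- Timing: the drugs are allowed during the treatment period. Inclusion criterion (e) rules out IBS-D medication in the week before entry. The analysis section itself contrasts this model with the one that holds only baseline variables.
- Trigger: intolerable symptoms or dissatisfaction with the effect. The text names TXYF; I read it as the blinded study product in either arm.
- Link to the outcome: the primary outcome is symptom severity on the IBS-SSS, the same construct that triggers use, and the permitted drugs are active treatments for IBS.
- The trial's own hypothesis: the Sample size section assumes response in 73% on TXYF and 43% on placebo, a difference of 73 − 43 = 30 percentage points. If that is right, symptom-driven use should also differ between arms.

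The claim that allocation does not affect use is therefore incompatible with the rule for use, unless TXYF changes neither symptoms nor perceived efficacy.

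**How far can the estimate move?** In a linear model of outcome on arm, adding an indicator of use changes the arm coefficient by an exact amount:

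unadjusted − adjusted = (coefficient of use) × (use on TXYF − use on placebo).

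Neither factor is in the documents, so what follows is an illustration with every parameter assumed. There are 1,000,000 simulated patients per scenario, and the outcome has a within-arm SD of 1 before any drug effect. The TXYF effect is −0.50 SD (lower is better). The mid-treatment and final scores share a severity component (0.8 × a common standard normal, plus independent noise with SD 0.6), so their within-arm correlation is 0.8² = 0.64. The log-odds of use are −1.2 + slope × mid-treatment score. Use lowers the final score by 0, 0.3 or 0.6 SD.

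| Benefit of drug (SD) | Slope | Use, TXYF v placebo | Coefficient of use | Unadjusted | Adjusted | Change relative to unadjusted |
|---|---|---|---|---|---|---|
| 0 | 1 | 19.2% v 27.0% | +0.549 | −0.501 | −0.459 | 8% nearer zero |
| 0 | 2 | 20.2% v 32.4% | +0.810 | −0.497 | −0.398 | 20% nearer zero |
| 0.3 | 1 | 19.4% v 26.8% | +0.245 | −0.475 | −0.457 | 4% nearer zero |
| 0.3 | 2 | 20.2% v 32.4% | +0.508 | −0.465 | −0.403 | 13% nearer zero |
| 0.6 | 1 | 19.3% v 26.9% | −0.052 | −0.458 | −0.462 | 1% further from zero |
| 0.6 | 2 | 20.4% v 32.4% | +0.210 | −0.424 | −0.399 | 6% nearer zero |

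Check of the second row: 0.810 × (0.202 − 0.324) = −0.099, and −0.497 − (−0.398) = −0.099; 0.099 / 0.497 = 20%.

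Two opposing parts are at work. If the drugs help and placebo patients take more of them, blocking that path enlarges the estimated benefit of TXYF. Use also marks patients who were doing badly, and conditioning on that marker shrinks the benefit. In the fifth row the two nearly cancel. In the second row the drug is inert and only the shrinkage remains.

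With slope 0 (use unrelated to symptoms, about 23% in each arm), or with a true TXYF effect of zero, adjusted and unadjusted estimates agree within simulation error. The logistic model was not simulated; there the argument rests on the structure alone.

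**The case against.** The affected model is one of two adjusted analyses, both planned only where appropriate. The simple regression, the chi-squared test and the baseline-adjusted model do not use the covariate, and neither does the sample size. The protocol defers to a statistical analysis plan that is not shown and that may rank the analyses. All of this stands and limits the reach of the point. It does not remove it, because the protocol itself states the covariate and a wrong reason for it, and does not say which analysis carries the conclusion.

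It can also be said that the bias is conditional and, in most of the scenarios above, conservative. That stands too. There is no bias in this model under a true null, and the largest attenuation assumes that the added drug does nothing.

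Two rescues of the wording fail. Blinding equalises the rule for taking other drugs between arms, but not the symptoms that feed the rule. Reading the term as medication at baseline does not fit the section that bears the same title, the entry criterion, or the contrast with the baseline-only model.

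A reader might infer that the trial's main result is biased, or that the adjusted effect must be too small. The documents support neither: the other analyses are sound on this point, and nothing in the text fixes the direction.

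**Conclusion.** The concern holds for the second adjusted analysis. The stated premise contradicts the protocol's own condition for using concomitant treatment. If TXYF affects symptoms or perceived efficacy, that model will in general give neither the ITT effect nor a clean direct effect, for the IBS-SSS score and, through the shared covariates, for the response rate. Its size and direction cannot be determined from the document. The range from almost no change to about 20% attenuation relative to the unadjusted effect rests wholly on the assumed rates, slopes and drug effects, and should not be quoted as an expected bias. The protocol should be corrected, but the point does not put the trial's other analyses in doubt.

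**What to change.** - Remove concomitant treatment from the covariates of both the linear and the logistic models.
- Strike the statement that allocation does not affect it, so that the analysis section agrees with the Concomitant treatment section.
- Adjust only for variables measured before randomisation.
- Report concomitant IBS-D medication by arm from the CRF.

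Optionally, add a sensitivity analysis that treats such use as an intercurrent event under a stated strategy, for example counting it as non-response for the responder outcome. That is a choice of estimand, not a correction, and it would leave the continuous score needing its own strategy.

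The cost is analysis wording only. Name, dosage and duration of these drugs are already recorded, and data collection, the rule for use and the sample size stay as they are.

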## Methods/design

### Study design

This is a randomized, multiple-blind, placebo-controlled superiority trial, and the protocol for this trial has been prepared following the Standard Protocol Items: Recommendations for Interventional Trials (SPIRIT) guidelines (see Additional file 1) [25]. The eligible participants will be allocated randomly into the experimental or placebo control group in a ratio of 1:1. Both groups will have an 8-week intervention followed by a 3-month follow-up period. This trial protocol has been registered in the ISRCTN registry (Reference number: ISRCTN12453166) on the 23 March 2021. A flow diagram of the trial is shown in Fig. 1.

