### Sample size

According to previous studies [37], it is estimated that TXYF can produce efficacy response (according to IBS-SSS) in 73% of participants with eight weeks treatment. Under the same treatment duration and evaluation criteria used in this trial, no results of placebo treatment of IBS-D were found. However, based on previously published relevant studies [38, 39], we expect TXYF to have a 30% higher response rate than placebo in the primary outcome, and superiority margin is expected to be 10% (*δ* = 10%). The ratio of the TXYF group to the control group was 1:1. So, the total sample size of 96 is based on the following formula [40], when *α* = 0.05, power = 0.8, and the estimated loss of participants is 10% [31]. That is, the number of participants to be enrolled in the trial should be 48 in each group.
$$ n={\left({Z}_{1\hbox{-} \alpha / 2}+{Z}_{1\hbox{-} \beta}\right)}^2\left[{P}_1\left( 1\hbox{-} {P}_1\right)+{P}_2\left( 1\hbox{-} {P}_2\right)\right]/{\left(P 1\hbox{-} P 2\hbox{-} \delta \right)}^2 $$

Where *n* denotes the sample size of each group, the value of *Z*_*1-α*_ and *Z*_*1-β*_ needs to consult the Z value table, *P*_*1*_ denotes the rate of the experimental group and *P*_*2*_ represents the rate of the control group, and *δ* represents the superiority margin. Therefore, when calculating the sample size of this trial, the value of *Z*_*1-α*_ is 1.96, the value of *Z*_*1-β*_ is 0.842, the value of *P*_*1*_ is 73%, the value of *P*_*2*_ is 43%, and the value of ***δ*** is 10%.

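### The sample-size section uses a 10-point superiority margin that the planned chi-squared test ignores, and the 48 per group fits the test, not the margin

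*Protocol article*

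**What the plan says.** Under Study design the protocol describes a "placebo-controlled superiority trial". No null or alternative hypothesis is written out there.

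Under Sample size, "it is estimated that TXYF can produce efficacy response (according to IBS-SSS) in 73% of participants with eight weeks treatment". The authors continue that "we expect TXYF to have a 30% higher response rate than placebo in the primary outcome", so the placebo rate is set at 43%, and that the "superiority margin is expected to be 10" per cent. The margin δ is subtracted from the expected difference in the denominator of the formula. The other settings are two-sided α = 0.05 (z = 1.96) and "power = 0.8, and the estimated loss of participants is 10" per cent. The stated result is 48 per group, 96 in total.

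Under Primary outcomes, response is defined from IBS-SSS severity levels, and the response rates are to be compared. No margin is mentioned.

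Under Statistical description and statistical analysis methods, "For primary and secondary categorical outcomes, differences will be compared using chi-squared tests", with logistic regression where needed. Treatment effects get 95% confidence intervals, and a two-tailed P-value of at most 0.05 counts as significant. The margin does not appear, and no decision is tied to the confidence interval.

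**The concern.** Subtracting δ from the expected difference is how one sizes a test whose null is a difference of 10 points or less. An ordinary chi-squared test has a null of no difference. The protocol thus sizes one question and tests another. Success on the response rate could be read two ways, and a P-value below 0.05 satisfies only the weaker of them.

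If the margin is meant seriously, superiority could be declared on data compatible with a benefit of a few points. If it is not meant seriously, the sample-size justification describes a test that the analysis section does not plan. In either case, the reader cannot tell which claim the 80% power supports.

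**Working it through.** **Inputs** (all from Sample size): P1 = 0.73, P2 = 0.43, δ = 0.10, z-values 1.96 and 0.842, loss 10%, 48 enrolled per group. With 10% loss, 48 × 0.9 = 43.2, so about 43 evaluable per group. The results below are given for both 43 and 48.

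**The plan's own figure.**

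- Variance term: 0.73 × 0.27 + 0.43 × 0.57 = 0.1971 + 0.2451 = 0.4422.
- Multiplier: (1.96 + 0.842)² = 7.851.
- With the margin: n = 7.851 × 0.4422 / (0.30 − 0.10)² = 3.472 / 0.04 = 86.8, so 87 evaluable **per group**.
- After 10% loss: 86.8 / 0.9 = 96.4, or 86.8 × 1.1 = 95.5. This is about 96 per group, whereas the protocol has 96 in total. The formula defines n as the size of each group, so the stated 48 is not reproduced.
- With δ = 0 in the same formula: 3.472 / 0.30² = 38.6, so 39 evaluable per group (44 after loss). With the pooled variance under the null, which matches the chi-squared test: [1.96 × √(2 × 0.58 × 0.42) + 0.842 × √0.4422]² / 0.30² = 41.3, so 42 per group (47 after loss).

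**Where the two rules part**, with the placebo rate near 43%, an uncorrected chi-squared test and a Wald interval:

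| Evaluable per group | Responders, TXYF v placebo | Difference (points) | P | Lower 95% limit (points) |
|---|---|---|---|---|
| 43 | 28 v 18 (first significant) | 23.3 | 0.031 | 2.8 |
| 43 | 31 v 18 (first above the margin) | 30.2 | 0.005 | 10.3 |
| 48 | 31 v 21 (first significant) | 20.8 | 0.041 | 1.3 |
| 48 | 35 v 21 (first above the margin) | 29.2 | 0.004 | 10.3 |

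For the first row: SE = √[(0.651 × 0.349 + 0.419 × 0.581) / 43] = 0.1046, and 0.2326 − 1.96 × 0.1046 = 0.028. Results of 28 to 30 responders (43 per group) or 31 to 34 (48 per group) would be significant without meeting the margin.

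**Probability of each outcome in favour of TXYF**, by exact binomial enumeration:

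| True rates | Evaluable per group | Chi-squared significant | Lower limit above 10 points |
|---|---|---|---|
| 53% v 43% | 43 | 14.5% | 3.7% |
| 53% v 43% | 48 | 16.7% | 3.6% |
| 73% v 43% | 43 | 82.6% | 54.1% |
| 73% v 43% | 48 | 85.8% | 58.1% |

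At 43% v 43% the chi-squared test favours TXYF in 2.6% (43 per group) or 2.5% (48 per group) of trials.

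The normal approximation for the margin rule is Φ(0.20 / √(0.4422/n) − 1.96). It gives 50% at n = 43 and 55% at n = 48, hence the range of about 50% to 58%.

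**The case against.** Four points can be made for the protocol, and most of their substance stands.

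First, a reader might infer that the trial is sized to show superiority by more than 10 points. The documents do not support that. The formula contains the margin, but the number reached does not follow from it. At 48 per group the margin has roughly even odds of being met.

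Second, a reader might infer that the planned test is underpowered or that its false-positive rate is 14.5% to 17%. Neither holds. At the assumed rates the chi-squared test exceeds the stated 80% power, and with no true difference it errs in favour of TXYF about 2.5% of the time. The 14.5% to 17% is the chance of detecting a real 10-point benefit. It is an error only for a claim that the benefit exceeds 10 points.

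Third, the protocol nowhere writes the margin out as a null hypothesis or says that superiority by more than 10 points will be claimed, and the word superiority under Study design fits a test of no difference equally well. This is true. Even so, a quantity called a superiority margin and subtracted from the expected effect has no other function in the formula.

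Fourth, an analysis plan that is not shown may hold a margin rule, and the promised 95% intervals would let readers check the margin. But the protocol has not left the choice open: it names the test and the significance threshold, and neither uses the margin. A rule elsewhere would still leave these two sections in conflict.

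**Conclusion.** The inconsistency is real and lies between two statements in the same document. The margin enters the sample-size formula but not the test or the significance rule, so a P-value of 0.05 or less establishes superiority over placebo and not superiority by more than 10 points. In practical terms, an observed difference of about 21 to 23 points is enough for significance, while about 29 to 30 points is needed to clear the margin.

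The planned chi-squared analysis is sound for the ordinary no-difference question, and the planned enrolment supports it. What cannot stand is the margin alongside that analysis and that number: 48 per group is about half of what the margin formula gives.

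The figures assume the protocol's 73% and 43%, between 43 and 48 evaluable per group, Wald limits and a chi-squared test without continuity correction. With a continuity correction, the zero-difference test needs 48 evaluable per group, or 54 after loss, so the statement that 48 enrolled is enough applies to the uncorrected test.

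**What to change.** Before unblinding, let one hypothesis govern both sections.

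- **Option 1.** Set δ to 0 under Sample size and restate the calculation for the two-sided test of no difference: 39 to 42 evaluable per group, 44 to 47 after 10% loss, so the planned 48 suffices. State that the chi-squared test is uncorrected, and claim only superiority over placebo. The test, enrolment and conduct stay as they are. The cost is giving up a stated margin after recruitment began in April 2021, so the change should be dated, explained and made blind to allocation.
- **Option 2.** Keep the margin. State in the analysis section that superiority is claimed only if the lower 95% limit of the response-rate difference exceeds 10 points, name the interval method, and restate the power at 48 per group as about 50% to 58%. The cost is that lower stated power. Restoring 80% would take 87 evaluable per group, or about 96 to 97 enrolled per group.

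Either option is an amendment of wording that can go through the ethics committee and registry route described under Ethics. Changing the test without restating the sample size would leave the stated 80% power wrong for the margin.

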### Ethics

This trial will be completed in accordance with the ethical principles in the Declaration of Helsinki and the Good Clinical Practice (GCP) Guideline. It has been approved by Medical Ethics Committee from FSH-BUCM approved on 4 February 2021 (ref: FZY LK-2021-002). CEBCM-BUCM will monitor and audit this trial.

If the trial’s protocol needs to be amended, the revisions will be discussed, communicated and concluded by the main investigators. The revised protocol will also be submitted to the Medical Ethics Committee for approval, and an application for revisions will also be submitted to the trial registry.

## Discussion

Irritable bowel syndrome is the most common functional gastrointestinal disorder characterized by abdominal pain/discomfort which is relieved by defecation and associated with altered stool frequency and/or consistency, in the absence of structural, microbiological, and biochemical abnormalities [2, 7]. The occurrence of this disease is not associated with structural or biochemical abnormalities that are detectable with the current routine diagnostic tools [42]. IBS-D with a high population prevalence that accounts for about 40% of all IBS patients. IBS-D significantly reduces the quality of life of patients and affects the patient’s daily activities and mental health. The specific pathogenesis of IBS-D has not been clarified clinically, and no specific therapeutic medications that can treat all the symptoms of IBS-D have been found.

IBS-D belongs to the category of diarrhea in TCM [14]. According to the diagnostic criteria for TCM syndromes [26], IBS-D can be divided into multiple syndrome types, such as Liver Depression and Spleen Deficiency Syndrome, Spleen Deficiency and Dampness Excess Syndrome (Pixu Shisheng Zheng), and Spleen-yang and Kidney-yang Deficiency Syndrome (Pishen Yangxu Zheng). Of these, Liver Depression and Spleen Deficiency Syndrome account for the highest proportion (85.6%) of patients with IBS-D [43]. Some herbal medicines may improve the symptoms of irritable bowel syndrome [44]. TXYF is one of the most commonly used Chinese herbal medicines for the treatment of IBS-D [16]. TXYF was first described by a book named *Danxi Xinfa* from Yuan Dynasty (1271-1368) and consists of *Atractylodes macrocephala Koidz.*, *Paeonia lactiflora Pall**.*, *Citrus × aurantium L**.*, and *Radix saposhnikoviae*. An animal experiment demonstrated that TXYF could increase the pain threshold and decrease the number of fecal pellets in IBS rats [45]. Also, TXYF has been shown in a clinical trial to demonstrate the therapeutic effects of anti-pain and anti-diarrhea on IBS-D patients [46].

Although some relevant studies have been carried out to verify the therapeutic effects and safety of TXYF in the treatment of IBS-D, to the best of our knowledge, the high-quality clinical trial is still lacking and not enough. The trial will allow in-depth analyses of mediating and moderating effects for different outcomes of TXYF in the treatment of IBS-D. Evidence regarding the therapeutic effects and safety of TXYF will be provided, and if effective and safe, this has the potential to be implemented in routine care to relieve the symptoms of IBS-D and improve the overall quality of life of patients. Success of this trial will present the justification and impetus for conducting a large-scale clinical trial to further consolidate the evidence for the use of TXYF in the treatment of IBS-D.

In conclusion, the results of this trial are expected to provide a high-quality and reliable evidence for the therapeutic effects and safety of the Chinese herbal formula TXYF for the treatment of IBS-D patients who also meet the diagnostic criteria of Liver Depression and Spleen Deficiency Syndrome.

